#### Economic analysis

The health economic analysis plan (HEAP) will be approved by the trial committees and will be published on the OSF before data-lock. Using all primary and secondary vocational, treatment-related, social and health outcomes, the analysis will determine whether IPS has a positive net benefit and is cost-effective compared to TAU. Using a cost-benefit ratio, a primary social cost-benefit analysis (CBA) will estimate the extent of additional monetised benefits accrued by the public and the Exchequer from investing in IPS. Costs and benefits will be analysed at the patient level, before and after exposure to IPS and TAU.

Taking an NHS and patient perspective, a secondary cost-effectiveness analysis (CEA) will compare outcomes at baseline and 18 months after trial enrolment to calculate the additional cost per quality-adjusted life-year (QALY), using mortality data and utilities estimated using the EQ-5D-5 L. An incremental cost-effectiveness ratio (ICER) will be estimated to determine whether IPS is cost-effective from the perspective of the health and social care sectors.

Outcomes from national registries will be used to estimate net tax revenue benefits accrued to the Exchequer, along with wider societal and economic benefits, and QALY gains. Official government fiscal, economic and social monetary values will be applied to the difference in events observed pre and post enrolment between the control and the intervention arms. For example, hospital activity will be valued by attaching average unit costs per episode derived from the Personal Social Services Research Unit (PSSRU) [28] or the national reference sheet [29] and criminal activity will be valued using the Home Office social and economic costs of crime [30].

The unit costs of IPS at each site will be estimated from information from the provider on site delivery using a Staff Time Survey (STS) of direct and indirect time spent on delivering IPS and delivering research. This will be conducted on three occasions during the study (i.e. at 6 months, 12 months and 18 months) to remove noise from the data collection exercise. The unit costs of TAU (including JCP appointments) will be calculated for both the control and the intervention arms of the trial using the Universal Credit Full Service (UCFS) strategic extract for Universal Credit claimants and the DWP Labour Market System (LMS) for legacy benefit claimants. We will work towards incorporating the costs of referrals to other labour market programmes, such as the WHP, using the same data sources.

All costs will be multiplied by the market forces factor (MFF) developed by the NHS to adjust for the unavoidable geographical cost differences by site and differential labour and building costs.

The within-trial primary and secondary analysis will be conducted after all participants have been followed-up for 18 months after trial enrolment. After completing the analysis and reporting of the within-trial primary and secondary economic analyses and sensitivity checks as specified in the HEAP, we envisage undertaking an exploratory longer-term economic analysis phase of the national registry data at 3 years and 6 years, subject to approval for a protocol amendment.

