#### Social and health

For the economic analysis, the following social and economic outcomes will be included:
Welfare payments (i.e. Job Seeker’s Allowance (JSA); Income Support (IS) Employment and Support Allowance (ESA); Universal Credit (UC); Housing Benefit (HB) and Tax Credits (TC))NHS hospital attendances and admissions (A&E, outpatient and inpatient)EuroQol 5-dimension, 5-level health survey (EQ-5D-5 L)MortalityConvictionsPrison sentences

JSA, IS, ESA, UC and HB welfare payments will be determined from the dates of starting and stopping receipt of each benefit type, or changes to levels of payment of each type, recorded in the following DWP databases: National Benefits Database (JSA, IS and ESA); and Universal Credit Official Statistics (UC), Housing Benefit Extract (HB). Tax Credit spells and amounts will be determined by use of HMRC’s General Matching System (GMS).

Hospital care will be recorded by Hospital Episode Statistics (HES; PHE is the data controller). The Office for National Statistics’ (ONS) register of births and deaths will record mortality.

Convictions and prison sentences will be recorded from extracts from the Police National Computer (PNC) and the National Offender Management Information System (p-NOMIS), respectively (both operated by the Ministry of Justice).

The EQ-5D-5 L [26] is a brief generic scale recording mobility, self-care, usual activities, pain/discomfort, anxiety/depression, with a 0 to 100-point vertical visual analogue scale (VAS) measuring overall health status. Site clinicians will complete this measure during personal interviews at baseline, 6 months, 12 months and 18 months and exit. HES, DWP and HMRC welfare payments, PNC and p-NOMIS data will be recorded from randomisation to the end of follow-up. For data modelling, we will also record these outcomes for 18 months prior to randomisation.

The schedule of enrolment, allocation, interventions and assessments is summarised in Table 1.

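### The market forces factor is applied to all costs, including IPS costs already estimated site by site; its scope should be limited to nationally priced cost lines

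*Protocol article*

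**What the plan says.** All of this is in the Economic analysis section of the protocol article unless noted.

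- **Scope of the factor:** "All costs will be multiplied by the market forces factor (MFF) developed by the NHS". No cost line is exempted.
- **Purpose:** "to adjust for the unavoidable geographical cost differences by site and differential labour and building costs".
- **IPS costs:** "The unit costs of IPS at each site will be estimated from information from the provider on site delivery". The instrument is a Staff Time Survey run at three time points. The article does not say whether the surveyed time is priced at local or national pay rates.
- **TAU costs:** "The unit costs of TAU (including JCP appointments) will be calculated for both the control and the intervention arms", from two DWP administrative sources.
- **Hospital care:** "hospital activity will be valued by attaching average unit costs per episode", taken from national sources. Crime is valued from Home Office figures.
- **Tax:** "Outcomes from national registries will be used to estimate net tax revenue benefits accrued to the Exchequer". Tax is therefore described as a benefit. The Vocational section takes tax and National Insurance from individual HMRC records.
- **Welfare:** the Social and health section says that "welfare payments will be determined from the dates of starting and stopping receipt of each benefit type", or from changes in payment level. Welfare payments are listed there among the outcomes for the economic analysis.

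The primary economic measure is a cost-benefit ratio from a social cost-benefit analysis. A health economic analysis plan (HEAP) is to be published before data-lock; it is not shown.

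**The concern.** The factor is there to handle price differences between places. It makes sense on a cost that does not yet reflect the place, such as a hospital episode valued at a national average. The rule as written also falls on IPS unit costs, which are built up separately at each site. If a site's figure already contains that site's salaries and premises costs, multiplying it by a site price index adds the same geographical difference a second time.

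IPS delivery is the investment that the primary cost-benefit analysis evaluates, so an error in its cost feeds straight into the ratio. It would also enter the incremental cost in the secondary cost-effectiveness analysis. A smaller problem of the same kind is that the rule does not say what happens to recorded cash amounts. A welfare payment has no site labour or building component; if it were entered as a cost and scaled, the analysed amount would differ from what was paid. The vocational effectiveness analysis is not affected.

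**Working it through.** The documents give no factor value, unit cost or projected ratio, so there is no stated figure to reproduce. The check is first one of logic and then of illustrative arithmetic.

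**Step 1: is there a purpose for which multiplying a local cost is right?**

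- *Aim: express national prices at local levels.* The national unit cost is multiplied once by the factor m. A cost already at local prices needs no multiplication.
- *Aim: remove price differences between sites.* A local cost is divided by m, not multiplied.
- *Multiplying a local cost by m* serves neither aim and widens the geographical difference.
- *Exception:* if surveyed staff time is first valued at national pay rates, multiplying by m adjusts it once, which is correct. The article does not say that this is done.

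**Step 2: size for a fully local IPS cost.** Let B be the benefit, C the correct IPS cost at local prices and m the factor. With benefits unscaled:

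ratio as planned = B / (m × C) = (B / C) / m.

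The values of m (0.95 to 1.30) and a true B/C of 1.5 are assumptions. The percentage change does not depend on the 1.5.

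| m | 1.5 / m | change in ratio, 1/m − 1 |
|---|---|---|
| 0.95 | 1.58 | +5% |
| 1.05 | 1.43 | −5% |
| 1.10 | 1.36 | −9% |
| 1.20 | 1.25 | −17% |
| 1.30 | 1.15 | −23% |

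**Step 3: dilution.** Two things shrink the effect.

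- *Only part of the denominator is local IPS cost.* If that share is s and the remainder is adjusted correctly, the ratio is divided by 1 + s(m − 1). With s = 0.5 (assumed) and m = 1.10, this is 1.05, a change of about −5% instead of −9%.
- *Only some sites have a factor away from 1.* With seven equal sites, one at m and six at 1.00, the pooled ratio is 7 × 1.5 / (6 + m). This gives 10.5 / 7.1 = 1.48 at m = 1.10 and 10.5 / 7.3 = 1.44 at m = 1.30.

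**Step 4: everything scaled alike.** If benefits are multiplied by m as well, the site's ratio is mB / mC = B / C, unchanged. The pooled ratio is also unchanged if all sites share the same ratio. Net benefit becomes m(B − C), so it is still rescaled: with C = 1, B = 1.5 and m = 1.10 it moves from 0.50 to 0.55.

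**The case against.** The strongest reply is that this is costing detail for the HEAP, that the sentence follows directly on the paragraph about IPS and TAU unit costs, and that its stated purpose confines it to service-delivery costs. On that reading, tax and welfare are outside it. It can also be said that a time survey yields hours, not money, so double adjustment is plausible but not shown.

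Much of this stands. Two stronger conclusions that a reader might draw are not supported:

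- *That the plan rescales actual tax and benefit amounts.* The rule concerns costs; the article calls tax revenue a benefit and lists welfare payments as outcomes. Welfare payments are caught only if they are entered as costs and the rule is read literally.
- *That the primary cost-benefit conclusion is distorted or reversed.* One can build a case in which a true ratio of 1.05 falls below 1 at an average factor of 1.10 (1.05 / 1.10 = 0.95), but both inputs are assumptions and only costs are scaled. With one of seven equal sites at 1.30 and the rest at 1.00, the average factor is 7.3 / 7 = 1.043 and 1.05 / 1.043 = 1.007, so there is no reversal. Factors below 1 move the ratio the other way.

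The HEAP argument does not dispose of the point. The article does not leave the scope of the factor open; it fixes it as covering every cost. A HEAP that follows the article inherits the problem, and one that narrows the scope departs from the article. The reading confined to service delivery does not help either, because IPS is a service-delivery cost.

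**Conclusion.** The point holds as a defect of scope. The article applies a site price multiplier to IPS costs that are estimated site by site and probably already carry site prices. Unless staff time is first priced at national rates, the resulting IPS cost is wrong by the factor m. The benefit/cost ratio is then divided by m when benefits are unscaled and the denominator is wholly local IPS cost, and by less when other correctly adjusted costs share the denominator.

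Both the direction and the size depend on site factors, pay rates and the treatment of benefits, none of which the documents give. The percentages above are illustrations, not estimates for this trial. For recorded cash amounts, the finding is only that the wording does not exclude them. This is worth correcting before data-lock because it bears on the primary economic measure.

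**What to change.** Replace the blanket rule, in the HEAP and in any update of the protocol, with one that names its scope:

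1. Apply the factor once, and only to service-delivery costs valued at national average unit costs or national pay rates. Hospital episodes are an example, as are Jobcentre and other TAU contacts if they are nationally priced.
2. Do not apply it to IPS costs built from local provider prices. Alternatively, value Staff Time Survey hours at national rates and then apply the factor once. State which of the two is used.
3. Do not apply it to recorded welfare, tax and National Insurance amounts, whichever side of the ratio they are entered on.

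Restricting the factor to NHS activity alone would be too narrow. It would leave nationally priced Jobcentre and TAU costs unadjusted beside locally priced IPS costs, with no reason given.

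The cost is a small amount of extra costing work: each cost line has to be classified as locally or nationally priced, or as a recorded cash amount. The classification should also say how the Home Office crime values are treated. No new participant data are needed.

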## Discussion

There is a complex and costly relationship between unemployment and alcohol and drug use and dependence. Harmful drinking is a risk factor for job loss [31] and, in some groups, unemployment predicts higher levels of drinking [32]. During economic recession, there is evidence that some people start to drink more and harmfully after losing their job [33]. Opioid use disorder (OUD) is associated with chronic unemployment [34, 35]. Untreated, OUD is associated with a reduced likelihood of job-seeking activity and finding work [36, 37].

IPS is a promising candidate intervention for people with alcohol and drug dependence who are seeking work; but there have been no formal trials. IPS-AD will provide policy-makers and treatment service commissioners with a definitive estimate of IPS effectiveness.

There will be several challenges to undertaking a pragmatic effectiveness RCT in community treatment services operated by the NHS, non-governmental and commercial providers. While ES are funded posts for the study, the keyworkers will be dividing their time between their primary clinical role and research tasks (e.g. completion of research measures). It may be challenging to secure the same rate of research follow-up between the two arms of the study. However, this will not affect the primary outcome because of the data-linkage design.

A strength of the study will be the causal mediation analysis and process evaluation to investigate IPS change mechanisms. For the former, the job-search self-efficacy concept (here measured by the JSSE-B instrument) has been frequently used in IPS research. One acknowledged limitation of the study is that we may not be able to determine competitive employment status for some participants who pursue self-employment due to the timeline for submitting self-assessment tax returns to HMRC. The current system in the UK is for a paper tax return to be submitted within 6 months after the end of a tax year and 9 months if the tax return is online. With the IPS-AD 18-month follow-up completed at the end of March 2021, determination of competitive employment would not be known for at least 10 months after this point (i.e. January 2022). The CBA and CEA questions for the sub-population of participants who register for self-employment and attain at least 7 h of paid work will, therefore, be addressed in a longer-term follow-up after the analysis of the primary outcome has been reported. Self-employment start, and end dates and associated earnings will be monitored using HMRC Connect and the UCFS databases where available.

In the UK, there is a high prevalence of unemployment among populations enrolled in treatment for alcohol and drug dependence, and a pressing need for effective employment interventions. If IPS is to prove effective, there will be NHS health savings, along with crime and employment benefits annually for the economy and the Exchequer [38]. We anticipate that the IPS-AD trial will make a substantial contribution to policy and practice.

## Trial status

IPS-AD was registered on ISRCTN (ID: ISRCTN24159790) on 1 February 2018. This article refers to version 1.0 of the approved protocol (23 May 2018). The first participant was enrolled in the study on 8 May 2018. The trial is ongoing and recruiting participants. The last day of participant recruitment will be 30 September 2019. The ISRCTN entry was edited on 20 June 2019 to show that participant recruitment is to be extended to 30 September 2019.

## Data Availability

A trial implementation guide developed by the study team is available from the corresponding author on request. This manuscript does not contain any data. Results from the trial will be submitted to academic journals and via press release and related communications via the sponsor.

## Abbreviations

A&E: Accident and emergency
AE: Adverse event
AUD: Alcohol use disorder
CBA: Cost-benefit analysis
CEA: Cost-effectiveness analysis
CI: Confidence Interval
CMH: Centre for Mental Health
Connect: HMRC database
CONSORT: Consolidated Standards of Reporting Trials
CPD: Continuing professional development
DHSC: Department of Health and Social Care
DMC: Data Monitoring Committee
DSM-5: *Diagnostic and Statistical Manual of Mental Disorders (5th edition)*
DWP: Department for Work and Pensions
EQ-5D-5 L: EuroQol 5-dimension, 5-level version
ES: Employment specialist
ESA: Employment and Support Allowance
FSS: Full Service System
GCP: Good Clinical Practice
GDPR: General Data Protection Regulation
GMS: General Matching System
HB: Housing benefit
HEAP: Health economic analysis plan
HES: Hospital Episode Statistics
HMRC: HM Revenue and Customs
ICER: Incremental cost-effectiveness ratio
IPS: Individual Placement and Support
IPS-AD: Individual Placement and Support for people with Alcohol and Drug dependence trial
IRAS: Integrated Research Application System
ITT: Intention-to-treat
JSA: Jobseeker’s Allowance
JSSE-B: Job Search Self-Efficacy: Behaviour scale
LDCS: Local Data Collection System
LMS: Labour Market System, DWP management information system
MFF: Market forces factor
MOJ: Ministry of Justice
NBD: National Benefits Database
NDTMS: National Drug Treatment Monitoring System
NHS: National Health Service
NIC: National Insurance contributions
NIHR: National Institute for Health Research
NINO: National Insurance Number
ONS: Office for National Statistics
OR: Odds ratio
OSF: Open Science Framework
OUD: Opioid use disorder
PCF: Participant Consent Form
PHE: Public Health England
PI: Principal investigator
PIS: Participant Information Sheet
PNC: Police National Computer
p-NOMIS: Prison National Offender Management Information System
PPI: Patient and public involvement
QALY: Quality-adjusted life-year
RCT: Randomised controlled trial
REGG: Research Ethics and Governance Group
RTI: HMRC Real Time Information system
SAP: Statistical analysis plan
SCID-5-CV: Structured Clinical Interview for DSM-5 Disorders – Clinician Version
SF: Social finance
SHBE: DWP Housing Benefit database
SPIRIT: Standard Protocol Items: Recommendations for Interventional Trials
STS: Staff Time Survey
TAU: Treatment as usual (standard employment support)
TIDierR: Template for Intervention Description and Replication
TOP: Treatment Outcomes Profile
TSC: Trial Steering Committee
UC: Universal Credit
UCFS: Universal Credit Full Service Strategic Extract
UCStats: Universal Credit Official Statistics
VAS: Visual analogue scale
WPLS: Work and Pensions Longitudinal Study, DWP database
